# Overview

- 1. **Schema**

|  | Patients with chronic respiratory failure receiving NPPV during outpatient visits | | | | | | | |  |
| --- | --- | --- | --- | --- | --- | --- | --- | --- | --- |
|  |  |  |  |  |  |  |  |  |  |
|  | During a routine outpatient visit, the attending physician or physician in charge will provide an overview of the study, to seek for patients who are willing to participate in the research | | | | | | | |  |
|  |  |  |  |  |  |  |  |  |  |
|  |  | Researcher explains the research overview, consenting participants fills out the consent form and are registered | | | | | |  |  |
|  |  |  |  |  |  |  |  |  |  |
|  | At enrollment (baseline)  Primary endpoint: Number of hospitalizations, number of hospital days, and number of unscheduled outpatient visits in the past 3 months  Secondary endpoints: SGRQ score, EQ-5D index, SCAQ responses, respiratory function test, and 6-min walk test | | | | | | | |  |
|  |  |  |  |  |  |  |  |  |  |
|  |  |  |  |  |  |  |  |  |  |
|  |  |  |  |  |  |  |  |  |  |
|  |  | Allocation (allocation adjustment factor: facility) | | | | | |  |  |
|  |  |  |  |  |  |  |  |  |  |
|  |  |  |  |  |  |  |  |  |  |
| Intervention group:  Usual outpatient care + tele-nursing intervention program | | | | |  | Control group:  Usual outpatient care | | | |
|  |  |  |  |  |  |  |  |  |  |
|  |  |  |  |  |  |  |  |  |  |
| Regular outpatient care (once/month)   1. Medical treatment by a physician 2. Health consultation and information by nurses   Remote nursing intervention program (1 time/day, 3 months)  Remote monitoring  Once a day  Observation of information input to the tablet  Input items: Vital signs, respiratory symptoms, food intake, excretion, medication, and physical symptoms other than respiratory symptoms  2. Health counseling and information provision  Health consultation and information provision via videophone once a day for approximately 30 min when triggers are applicable or when the participant wishes | | | | |  | Regular outpatient care (once/month)   1. Medical treatment by a physician 2. Health consultation and information by nurses | | | |
|  |  |  |  |  |  |  |  |  |  |
|  |  |  |  |  |  |  |  |  |  |
|  |  |  |  |  |  |  |  |  |  |
|  |  |  |  |  |  |  |  |  |  |
|  |  |  |  |  |  |  |  |  |  |
|  |  |  |  |  |  |  |  |  |  |
|  |  |  |  |  |  |  |  |  |  |
|  |  |  |  |  |  |  |  |  |  |
|  |  |  |  |  |  |  |  |  |  |
|  |  |  |  |  |  |  |  |  |  |
|  |  |  |  |  |  |  |  |  |  |
|  |  |  |  |  |  |  |  |  |  |
|  |  |  |  |  |  |  |  |  |  |
|  |  |  |  |  |  |  |  |  |  |
|  |  |  |  |  |  |  |  |  |  |
|  |  |  |  |  |  |  |  |  |  |
|  | [Three months after enrollment]  Primary endpoint: Number of hospitalizations, number of hospital days, and number of unscheduled outpatient visits in the past 3 months  Secondary endpoints: SGRQ score, EQ-5D index, SCAQ responses, respiratory function test, and 6-min walk test | | | | | | | |  |
|  |  |  |  |  |  |  |  |  |  |
|  |  |  |  |  |  |  |  |  |  |
|  |  |  |  |  |  |  |  |  |  |
|  | [Expected effects of the intervention]  The tele-nursing intervention program is expected to ameliorate the self-management behavior of the intervention group and to significantly improve the primary and secondary endpoints compared with the control group | | | | | | | |  |
|  |  |  |  |  |  |  |  |  |  |
|  |  |  |  |  |  |  |  |  |  |

- 1. **Objective**

The purpose of this randomized, controlled trial is to evaluate the effect of a tele-nursing intervention program utilizing Information and Communication Technology (ICT) on the prevention of acute exacerbations in patients with chronic respiratory failure receiving noninvasive positive-pressure ventilation (NPPV) in home care.

- 1. **Participants**

We included patients aged at least 20 years, with chronic respiratory failure, receiving NPPV, attending the outpatient Department of Respiratory Medicine at Tohoku University Hospital and cooperating institutions, without cognitive impairment, and who provided informed consent for study participation.

- 1. **Number of planned cases and study period**

(1) Number of planned cases

Based on previous literature, the average number of visits to the emergency department due to acute exacerbation of chronic respiratory disease in patients who use and do not use NPPV is 2.4 and 1.6 times/year, respectively; hence, we assume that the number of visits will improve by 1.0 time/year. The significance level will be 5%, the power will be 80%, and the standard deviation of the number of visits assumed to reduce the occurrence of acute exacerbations will be 1.0 visit/year. In addition, the proportion of included patients who drop out in the middle of the study is assumed to be 10% of the total number of patients; in addition, the intervention and control groups will comprise 17 patients each. Therefore, the planned number of cases for this study is 34.

(2) Research period

After Ethics Committee approval (May 2017) - March 2019

(3) Registration period

After Ethics Committee approval - October 2018

- 1. **Contact information**

(1) Eligibility criteria, treatment modification criteria, and other criteria requiring clinical judgment, registration procedures, and case record form (CRF) entry

Research Secretariat

Doctoral Program: [name]

Department of Cancer Nursing, Division of Family Support Nursing, Department of Health Sciences, Tohoku University Graduate School of Medicine

Tel: [name]

E-mail:　[contact]

# Objective

The effectiveness of an ICT-based tele-nursing intervention program for patients with chronic respiratory failure undergoing NPPV in home care will be examined in terms of the number of readmissions and occasional visits due to acute exacerbations or chronic respiratory diseases, with readmission and occasional visit rates as primary endpoints.

# Background and rationale for the research plan

# Background

In recent years, Japan's population has been aging at a rate unparalleled in other countries, and by 2025, when the baby boom generation will be aged at least 75 years, there would be a need to establish a community-based comprehensive care system that will enable people to continue living their lives in their familiar neighborhoods until death, even if they require nursing care [1-3]. In addition, approximately 300,000 beds are planned to be transferred from hospitals to home care centers by 2025 [4], and the shift from hospital-based to community-based care is being accelerated [5]. Telemedicine utilizing ICT is a means to support the operation of the community-based comprehensive care system [6]. In Japan, ICT-based telemedicine is considered to contribute greatly to the creation of new wealth and efficiency of production activities, thereby improving living conditions; moreover, the government is considering the application of measures to utilize ICT for the super-aging society [7]. The American Thoracic Society and European Respiratory Society recommend integrated care for patients with chronic respiratory diseases [8,9] and the application of the principle of "providing appropriate care that meets the individual needs of patients at the right time and place" [10]. Based on this principle, the practice of telemedicine has spread remarkably in Europe and the United States and has been effective in reducing home health care costs by providing the same quality of medical and nursing assistance to patients, regardless of where they reside [11]. Meanwhile, telemedicine in Japan began in the 1970s, and since then, the foundation of telemedicine has been established through tele-imaging and tele-intraoperative pathology diagnosis between distant doctors, telemedicine between distant doctors and patients [12-15], and tele-nursing, in which nurses provide health consultation to patients [16-18]. Tele-nursing, in particular, involves biometric data collection for the purpose of improving the health of patients in need of health management and provides opportunities for accurate health counseling and guidance as well as an understanding of patient health status [19]. In addition, the practice of telemedicine is gradually becoming more widespread because it can provide high quality health care by enabling interactive communication with patients via image and voice over a videophone to alleviate their concerns [20].

Chronic respiratory failure is defined as respiratory insufficiency that persists for more than 1 month [21]. The most common cause of chronic respiratory failure is chronic obstructive pulmonary disease (COPD), which accounts for 45% of patients with chronic respiratory failure [22]. According to a 2008 World Health Organization report [23], COPD is expected to become the third leading cause of death by 2030, and the number of patients with chronic respiratory failure is expected to increase in the future. The White Paper on Home Respiratory Care reported that many outpatients with COPD receive home oxygen therapy (HOT) and NPPV [24], indicating the advancement of home healthcare for patients with chronic respiratory failure. In addition, non-pharmacological therapies, such as respiratory rehabilitation and patient education on daily living activities, have become the mainstay of treatment, and a common treatment strategy has been established, regardless of the causative disease [23]. According to the American Thoracic Society and European Respiratory Society, respiratory rehabilitation is "a comprehensive medical intervention based on a thorough patient assessment, followed by exercise therapy, education, and behavior modification; it also involves the improvement of the physical and psychological status of patients with chronic respiratory disease and adherence to behaviors for long-term health promotion. NPPV is defined as the use of a nasal-mouth mask interface primarily during sleep, as a form of ventilatory support therapy for chronic respiratory failure, to reduce arterial blood gas levels, dyspnea, and morning headache and fatigue. Since it does not require tracheal intubation, patients can lead their daily lives without problems such as difficulty in speaking, eating, and drinking. The introduction of NPPV in patients with chronic respiratory failure has improved the life expectancy and significantly improved the quality of life (QOL) [25] of patients. However, chronic type II respiratory failure does not only involve hypoxemia due to impaired gas exchange, but also coexists with hypercarbia due to ventilatory failure [21]. In addition, patients with chronic respiratory failure receiving NPPV experience a decreased range of activity due to respiratory symptoms and pain when wearing masks, which is a disincentive to utilizing NPPV equipment and increases the risk of carbon dioxide (CO_2_) narcosis [27]. Patients with type II respiratory failure may be perceived as living the same daily life as patients with type I respiratory failure; however, in addition to developing hypoxia, they are prone to developing hypercarbia and therefore must learn to manage their more complex physical condition. It is assumed that patients who easily increase their oxygen level to cope with dyspnea or shortness of breath during an acute exacerbation may induce a high CO_2_ state, thereby triggering CO_2_ narcosis. Acquiring the knowledge and appropriate behavior to cope with respiratory symptoms will reduce the chance of inadvertent CO_2_ narcosis. In addition, patients with chronic respiratory failure receiving NPPV have poor respiratory function reserve and exercise tolerance and thus can easily develop acute exacerbations due to the common cold [23]. This can lead to deterioration of cardiac failure and other systemic conditions, which can be immediately fatal. Patients with chronic respiratory failure have respiratory symptoms, such as cough, sputum production, and dyspnea; hence, it is difficult to notice changes in acute exacerbations, which may lead to a delay in seeking medical attention, resulting in a more serious situation. Prolonged or repeated hospitalization leads to a decline in activities of daily living (ADLs), which in turn leads to a decline in QOL [25].

Acute exacerbation in patients with chronic respiratory failure is defined as a rapid worsening of respiratory symptoms, such as dyspnea, cough, sputum production, and respiratory failure status, and can occur when respiratory infection, air pollution, pneumothorax, right heart loading due to fatigue, psychological factors, excessive use of sleeping medication, inappropriate oxygen administration, or worsening of the underlying disease are combined to cause acute exacerbation [23] The literature detailing the causes of acute exacerbations in patients with chronic respiratory failure is scarce. According to the guidelines of COPD, a causative disease of chronic respiratory failure, 50-70% of acute exacerbations are caused by respiratory infections, including the common cold, 10% by air pollution, and approximately 30% by unknown causes [28]. Respiratory infections are caused by the indigenous bacteria *Haemophilus influenzae* and *Streptococcus pneumoniae*, whereas viral infections are caused by influenza viruses and adenoviruses. Air pollutants, such as ozone, nitrogen oxides, and suspended particulate matter less than 10 μm in diameter, can be inhaled from the air. Tobacco smoke, in particular, contains approximately 4,000 chemicals, 200 toxic substances, and more than 60 carcinogens, which become fine particles less than 2.5 μm in diameter, thereby creating an environment that can predispose patients to acute exacerbations [29]. Therefore, a smoke-free environment is required for patients with chronic respiratory failure [30]. Thus, the prevention of respiratory tract infections and avoidance of air-polluted environments are important countermeasures against acute exacerbations in patients with chronic respiratory failure. Respiratory tract infection prevention requires appropriate rest and sleep to improve the body's resistance to infection and nutritional management [23,30]. Other methods to eliminate local viruses and bacteria include wearing masks, washing hands and gargling, body hygiene, and inoculation with various vaccines [31] as specific preventive measures. Other effective measures against acute exacerbations include environmental adjustments, such as moderate temperature and humidification, the maintenance of physical activity such as respiratory rehabilitation, and drug therapy management [32-35]. In contrast, dyspnea is not a life-sustaining symptom. Nevertheless, dyspnea reportedly causes a vicious cycle of anxiety and fear about life support, leading to decreased physical activity and muscle weakness, which in turn exacerbates dyspnea [27]. Samantha et al. reported that patients with chronic dyspnea required that medical care providers furnish them with information about their daily life, such as "how to reduce shortness of breath" and "breathing exercises" [24]; thus, it can be inferred that these patients are living with anxiety while undergoing medical treatment. Samantha et al. reported that patients with chronic respiratory failure can avoid acute exacerbations through effective self-management using knowledge and skills, such as infection prevention, nutritional management, and respiratory rehabilitation, to cope with symptoms and to prolong the stable period [32].

In clinical practice, due to the shortened length of hospital stay, promotion of home care, and shortage of manpower, medical personnel provide treatment and examinations within limited time constraints; therefore, it can be inferred that information provision and health counseling with consideration for individual patients are lacking. Currently, pharmacotherapy for symptom improvement and non-drug therapies, such as information provision for knowledge acquisition and respiratory training for maintenance and improvement of physical endurance, are provided when patients are in the hospital and are continued during outpatient care. However, it has been reported that these therapies affect the course of respiratory symptoms if they are continued, not only during hospitalization but also during treatment at home [36]. Therefore, patients with chronic respiratory failure can prevent acute exacerbations and maintain their QOL if they understand and agree with the treatment at home, practice self-management, and lead their own daily lives. In Japan and overseas, there have been reports [37-39] on the implementation of respiratory rehabilitation and action plans for patients with chronic respiratory failure receiving HOT by nurses, and telemedicine services such as tele-nursing have been shown to be effective in preventing acute exacerbations and improving physical activity [16]. However, tele-nursing for patients undergoing NPPV for chronic respiratory failure, a more medically dependent condition, is considered to be a very important support for preventing acute exacerbations and maintaining QOL, albeit no firmly established evidence.

The purpose of this study is to examine the effectiveness of a tele-nursing intervention program to support the lives of patients with chronic respiratory failure receiving NPPV, incorporating non-pharmacological therapies such as proactive symptom management and infection prevention behaviors according to their physical and mental statuses. Currently, the average age of patients with chronic respiratory failure receiving NPPV is 72.6 years, and 80% of all patients are aged older than 60 years [24]. The aging of patients suggests that not only medical intervention but also social support is needed. However, there is no item in the criteria for caregiver certification that directly determines respiratory impairment; furthermore, patients with chronic respiratory failure can move if they exert themselves, and therefore, their caregiver certification tends to be lower than that of patients with other physical disabilities, thereby making it difficult to increase the amount of care support they need adequately. Given the possible decline in visual acuity and cognitive ability associated with population aging, life support tools that can more easily and clearly indicate changes in physical symptoms and are tailored to the physical condition ascertained are necessary for appropriate self-management [40]. Currently, patients with chronic respiratory failure under home care keep a medical diary to manage their physical condition, although it is necessary to apply electronic tools that provide remote patient guidance and health counseling while visualizing physical activity, vital signs, and other physical conditions to make patients more aware of the effects of treatment; moreover, educational tools that make it easier for patients to acquire knowledge and skills and to perform self-monitoring are also needed. Therefore, an electronic medical care diary should be created to enable patients to visualize their daily physical condition, and lifestyle guidance tailored to their individuality using the electronic medical care diary should be included in the tele-nursing intervention program. The information obtained from the electronic medical journal is shared between the patient and nurse, and when necessary, the patient can use the social networking service (SNS) function to communicate and to consult with the nurse via video call, in order to alleviate patient anxiety and fear during daily medical care. This is a necessary part of a tele-nursing intervention program. This study will enable patients receiving NPPV for chronic respiratory failure to safely self-manage their condition at home, thereby reducing dyspnea occurrence, improving health-related QOL, and reducing the number of readmissions and occasional outpatient visits due to acute exacerbations, as well as readmission and occasional visit rates.

# Scientific rationale of the study

Chronic respiratory failure is a condition in which respiratory failure is caused by irreversible changes in the respiratory organs, such as the lungs and airways, and persists for more than 1 month. Type I respiratory failure requires oxygen therapy, whereas type II respiratory failure requires ventilatory support therapy in addition to oxygen therapy. With the development of medical care in recent years, oxygen therapy and assisted ventilation therapy applications in home care settings have become remarkably widespread and are indispensable for maintaining and improving QOL. Patients with chronic respiratory failure have poor respiratory reserve and are prone to developing acute exacerbations; thus, respiratory rehabilitation and continued self-management after discharge from the hospital are essential for improving QOL, along with medical device management. Patients with chronic respiratory failure have dyspnea as the main symptom; however, dyspnea does not interfere with ADLs, and thus, they are able to receive home care through the management of their own health condition. The number of patients with chronic respiratory failure receiving home care is increasing, and the key to preventing acute exacerbations and maintaining patient health status is to continue self-monitoring, coping with dyspnea, and infection prevention. This study visualizes the physical condition of patients with chronic respiratory failure using a tablet terminal to help them manage their own health condition. We will develop a tele-nursing intervention program that provides remote monitoring, health counseling, and information and verify the effectiveness of the program in preventing acute exacerbations of chronic respiratory failure. For patients with chronic respiratory failure, repeated acute exacerbations cause a decline in physical activity and respiratory reserve, leading to a decline in QOL. In addition, this study is economically significant because it will help reduce medical costs by preventing acute exacerbations and re-hospitalization of patients with chronic respiratory failure via the enhancement of their home care maintenance. The ethical, scientific, and medical appropriateness of conducting this study will be reviewed by the Ethics Committee of Tohoku University Graduate School of Medicine, and approval will be obtained from the Director of the research institution.

# Selection policy for research participants

# Eligibility criteria

We will include patients with chronic respiratory failure undergoing NPPV, attending the outpatient Department of Respiratory Medicine at Tohoku University Hospital, and who have given consent to participate in the study based on the approval of the Ethics Committee of Tohoku University Graduate School of Medicine and Ethics Committee of each cooperating institution until March 31, 2019. Patients who meet all of the following eligibility criteria will be included.

(1) Patients with chronic type II respiratory failure lasting at least 1 month (with an arterial blood partial pressure of CO_2_ of 45 mmHg or higher), whose primary illness is a respiratory disease such as COPD or pulmonary tuberculosis sequelae, and who are receiving NPPV therapy [2].

(2) Since this study does not identify the type of respiratory disease, no disease stage can be established.

(3) Age at enrollment will be 20 years or older, and no upper age limit will be set, as the study will be open to anyone who is able to handle a tablet device.

(4) Gender is not an issue, as we will not alter the intervention based on gender.

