
The web-based program in the tele-nursing system consists of a patient site and a researcher site. The tablet terminal at the patient site has (1) a screen for recording daily physical condition, (2) a screen for video calls, (3) a screen for SNS input, and (4) a screen for respiratory rehabilitation information. The researcher's site will have (1) a list of the participant's telemonitoring data and (2) a screen for inputting comments. The researcher can check the participant's daily records and output the changes over time on a summary sheet.

The intervention period will be 24 weeks, and the number of ad hoc visits and readmissions during the past 12 and 24 weeks (primary endpoints) will be examined by the researcher at enrollment, 12 weeks after enrollment, and 24 weeks after enrollment, using the electronic medical record. At enrollment and at regular outpatient visits 12 and 24 weeks after enrollment, researchers will conduct a questionnaire survey about daily life, and perform respiratory function and 6-minute walk tests. In addition, activity meters will be checked 12 and 24 weeks after enrollment to collect data on the average number of steps and patient activity. Respiratory function and 6-min walk tests at enrollment as well as 12 and 24 weeks after enrollment will be performed by the researcher using equipment purchased using the research fund, since these tests are not covered by insurance and are outside the scope of usual medical care. Since the primary endpoints of this study are the number of emergency visits and rehospitalizations due to acute exacerbations of chronic respiratory diseases, the intervention will not be stopped in the event of worsening symptoms due to acute exacerbations. If the participant dies, the intervention is terminated because the study cannot continue. If a participant requests that the intervention be continued after their participation in the program, the intervention may be offered for an extended period of time, regardless of whether the participant is in the intervention or control group.

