# Research period

The research period will be from May 2017 (after approval by the Ethics Committee of Tohoku University Graduate School of Medicine) to March 2019.

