# Evaluation items and methods

# Primary endpoints

Since the purpose of this study is to verify the effectiveness of a tele-nursing intervention program for the prevention of acute exacerbations of chronic respiratory diseases, it is necessary to set the status of acute exacerbations as an evaluation item. Acute exacerbations cannot be determined simply by considering the number of temporary visits and rehospitalizations separately, and thus, the primary endpoints of this study are the statuses of temporary outpatient visits (rate and number of visits) and rehospitalizations (rate and number of hospitalizations) due to acute exacerbations in the past 12 and 24 weeks, as well as the reasons for the outpatient visits or hospitalizations at enrollment (baseline) and 12 weeks after enrollment. The data will be collected from the patients themselves at baseline, 12 weeks after enrollment, and 24 weeks after enrollment. However, if the patient's complaint is unclear, it will be collected from the patient's medical record.

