# Methods of data management and self-inspection

# CRF preparation

The researcher will complete and correct the entries on the CRF. The investigator will complete the CRF promptly after the completion of the intervention for each participant. Since the program lasts for 24 weeks, the CRF will be prepared after 24 weeks of intervention. Care should be taken to ensure that the primary and secondary endpoints are covered and that vital signs and information on how the daily evolution of the participant's condition can be clearly and concisely ascertained. In addition, as with the nursing record, videophone information should be recorded such that it can be understood.

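### The enrolment dates conflict, and neither allows every permitted enrolee to reach the 24-week primary endpoint before the study ends in March 2019

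*Protocol*

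**What the plan says.** Three dates govern the calendar.

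- **Registration close.** The Overview gives the registration period as "After Ethics Committee approval - October 2018", with no day of the month.
- **Study end.** The Overview gives the research period as "After Ethics Committee approval (May 2017) - March 2019", and the Research period section repeats the March 2019 end ("The research period will be from May 2017 (after approval by the Ethics Committee of Tohoku University Graduate School of Medicine) to March 2019").
- **Consent date.** The Eligibility criteria section describes the included patients as those who have consented on the basis of approval by the university committee and the "Ethics Committee of each cooperating institution until March 31, 2019".

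Follow-up per participant is 24 weeks throughout the body of the protocol. The programme overview states that "The intervention period will be 24 weeks". The survey schedule has a 24-week column. The Primary endpoints section says "The data will be collected from the patients themselves at baseline, 12 weeks after enrollment, and 24 weeks after enrollment". The CRF preparation section says "Since the program lasts for 24 weeks, the CRF will be prepared after 24 weeks of intervention".

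The Registration section enrols a patient when the consent form is submitted, so consent date and enrolment date can be treated as the same day.

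**The concern.** There are two problems.

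First, the document offers two candidate dates for the end of recruitment, five months apart. If both are meant as recruitment limits, a site cannot follow both.

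Second, neither date leaves 24 weeks before the end of March 2019 for everyone it admits. A patient who enters too late has either no 24-week assessment within the study period or a shortened one. Visits and readmissions by week 24 are primary outcomes. The Statistical analysis methods section compares numbers of visits and readmissions by t-test and rates by Fisher's exact test, with no stated allowance for unequal observation time. With 34 patients planned and a 10% dropout allowance, a few incomplete follow-ups are not negligible.

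The March 2019 end also leaves little or no time after the last 24-week visit to complete case report forms, which are prepared only once the 24 weeks are over, to submit them to the data centre and to analyse the data.

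**Working it through.** The protocol gives no derived timeline figure, so there is nothing to reproduce. The check is calendar arithmetic.

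**Inputs**
- Follow-up: 24 weeks = 24 × 7 = 168 days; the 12-week assessment = 84 days (programme overview, survey schedule, Primary endpoints).
- Study end: March 2019, taken at its latest reading, 31 March 2019 (Overview, Research period).
- Registration close: October 2018, day not given, so 1 to 31 October (Overview).
- Alternative consent limit: 31 March 2019 (Eligibility criteria).
- Planned enrolment: 34 (Planned number of cases).
- Assumption: even accrual from 1 May 2017. The protocol gives no accrual projection.

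**Latest workable enrolment dates**
- Week 24 by 31 March 2019: 31 March 2019 − 168 days = 14 October 2018.
- Week 12 by 31 March 2019: 31 March 2019 − 84 days = 6 January 2019.

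**Where week 24 falls**

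| Enrolled | Week 12 | Week 24 | Days past 31 March 2019 |
| --- | --- | --- | --- |
| 1 October 2018 | 24 December 2018 | 18 March 2019 | −13 (fits) |
| 14 October 2018 | 6 January 2019 | 31 March 2019 | 0 (last that fits) |
| 15 October 2018 | 7 January 2019 | 1 April 2019 | 1 |
| 31 October 2018 | 23 January 2019 | 17 April 2019 | 17 |
| 31 March 2019 | 23 June 2019 | 15 September 2019 | 168 |

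A patient enrolled on 31 October 2018 has 151 days, or 151/7 = 21.6 weeks, before the study ends. The shortfall is 17/168 = 10% of the intended follow-up.

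**Patients affected, if accrual is even**
- *Overview close, 31 October 2018.* 1 May 2017 to 31 October 2018 is 549 days, of which 15-31 October is 17. 17/549 = 3.1%; 0.031 × 34 = 1.05, about 1 patient.
- *Consent accepted to 31 March 2019.* 1 May 2017 to 31 March 2019 is 700 days, of which 168 fall after 14 October 2018. 168/700 = 24%; 0.24 × 34 = 8.2, about 8 patients without a 24-week assessment. Of those 168 days, 84 fall after 6 January 2019. 84/700 = 12%; 0.12 × 34 = 4.1, so about 4 of the 8 would also miss week 12.

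The range is therefore about 1 to 8 of 34, depending on which date governs. Faster accrual at the end would raise these numbers and faster accrual at the start would lower them.

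**The case against.** The strongest counter-argument is that the eligibility sentence is ambiguous. The date directly follows the mention of the ethics committees and coincides with the end of the research period, so it may state how long the approval runs. Only the Overview labels a date as the registration period, and that date is October 2018. On this reading the conflict between the two dates disappears, and the problem shrinks to about one patient overrunning by at most 17 days. Since the Overview gives months without days, enrolment that actually stopped by 14 October would fit. All of this is fair. It does not remove the overrun for 15-31 October, and the sentence would still need rewording, because it defines who is included and a consent limit is its more natural sense.

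A reader might also infer more than the documents support:

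- *That about a quarter of patients will lack the endpoint.* This needs the consent-limit reading, enrolment continuing past the Overview's October close, and even accrual. It is an upper scenario among the two readings, and about half of those patients would still reach week 12, which is also a primary time point.
- *That truncated counts will enter the t-test as if they were full 24-week counts and dilute the effect.* The protocol does not say that follow-up is cut off at the end of March 2019, or how incomplete follow-up is handled. Case report forms are to be prepared after 24 weeks, and a change of research period is listed among routine revisions, so an extension is at least as plausible as truncation. Detailed handling may also sit in an analysis plan that is not available here.
- *That the assumed effect is already small.* The sample-size section assumes a difference of 1.0 visit per year with a standard deviation of 1.0, which is a full standard deviation.
- *That late enrolment is expected.* The Registration section anticipates difficulty in reaching the required number and plans sequential enrolment. It does not say that entry will cluster at the end.
- *That the dates are left over from a 3-month design.* The schema does show a 3-month programme, which would fit an October close (31 October + 12 weeks = 23 January 2019). But an October-to-March gap is also roughly what 24 weeks needs at month precision, so the origin of the dates cannot be established.

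**Conclusion.** The point holds as a scheduling inconsistency that is wrong as written. With a 24-week endpoint and a study ending on 31 March 2019, enrolment after 14 October 2018 cannot be completed, yet the Overview permits up to 17 further days and the eligibility text may permit 168.

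The 14 October limit rests on the protocol's own dates, on the latest reading of the March 2019 end, and on counting 24 weeks from enrolment. The number of patients affected also rests on the assumption of even accrual and on which date governs.

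The consequence that can be asserted is missing or shortened 24-week primary data for patients admitted too late, with no rule stated for them. A bias of particular size or direction in the comparison cannot be asserted from this document. The dates should be corrected, but the design is not undermined.

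**What to change.** Choose one of two routes and make the Overview, the Eligibility criteria and the Research period section agree.

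1. **Keep the 31 March 2019 end.** State a single last-enrolment date, with a day, in the Overview and the eligibility section, no later than 14 October 2018. An earlier date, or a later study end, is needed to leave time for case report forms and analysis.
2. **Keep the later enrolment date.** Extend the research period in both places where it appears to at least 24 weeks after the last permitted enrolment: 17 April 2019 for a 31 October 2018 close, or 15 September 2019 for a 31 March 2019 close. Add time for case report forms and analysis.

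If 31 March 2019 is only the term of the ethics approval, reword the eligibility sentence to say so and let the registration period alone define the close.

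The cost depends on which date is kept. Under the October close it is about two weeks of enrolment (17 days) or a short extension. Keeping 31 March 2019 as a consent limit would need about 24 more weeks of study time. The section on changes to the protocol classes a change in the research period as a revision, its lighter category of change, which still requires approval by the institutions.
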